## 12.5 DECLARATION OF INTEREST

None of the chief or principal investigators has paid consultancies with the pharmaceutical companies involved in the trial, or other competing interest for the overall trial or in each study site.

## 12.6 ACCESS TO SOURCE DATA/DOCUMENTS

In addition to the clinical monitors, authorised representatives of the sponsor/CRO, an IEC/IRB or regulatory authority may visit the study site to perform audits or inspections, including source data verification. The investigator agrees to allow the sponsor and CRO representatives, including the monitor and study safety monitor, the DSMB, the IRB/IEC and regulatory authority direct access to source data and other relevant documents.

## 12.7 RISKS AND BENEFITS

### 12.7.1 Risks to Study Participants

#### 12.7.1.1 *Safety of the study drugs*

See section 7.2.1, Risks associated administration with artemether-lumefantrine, page 34 and section 7.2.2, Risks associated with pyronaridine-artesunate, page 35.

#### 12.7.1.2 *Procedures for participants developing acute respiratory symptoms during the trial*

The study will be conducted in an environment where national guidelines in each country may change during the course of the study that determines which patients are admitted in hospital or kept in isolation wards versus which patients with no or mild symptoms are asked to self-isolate at home. If after enrolment initially asymptomatic patients develop symptoms, or if symptoms worsen consistent with severe COVID-19, the participant will be asked to alert the study team by phone,

such that transport arrangements can be made for the participant to visit the study clinic and/or hospital or for a home visit.

### 12.7.1.3 Blood and tissue sampling

The additional protective measure used for sampling from COVID-19 patients is discussed in more detail in section 12.7.3.1, Biohazard containment to limit risks of SARS-CoV-2 transmission, page 65.

All examinations undertaken as part of this study will be non-invasive, with the exception of blood sampling and swabs. Blood sampling may be inconvenient to the participants and may cause minor discomfort and bruising. In some aspects of the trial, blood sampling has the potential to directly benefit the participants or their babies, as any malaria infection or anaemia detected as a result of the sampling will be treated. In other aspects of the trial, such as the immunological assays, will not be of direct benefit to the individual participants, but the potential knowledge gained will eventually be used to benefit all populations in areas where malaria and COVID-19 co-exist.

### 12.7.1.4 Maximum blood volume

In adults and older children above the minimum age of assent, a blood sample of no more than 20mL per sample will be taken at days 1 (enrolment) and day-28 (close-out) and 15mL on each of the five scheduled visits up to day 42 inclusive (day 3, 7, 14, 21 and 42) and during the extended follow at 3, 6, and 12 months. Thus the total cumulative volume of blood collected from each participant will be small (130.25mL in the first three months [0.25 mL at screening, 2 further blood draws of 20mL and 5 blood draws of 15mL in the first 42 days plus one 15mL blood draw at three months] and 160.25 mL in total over 12 months [two additional 15mL blood draws at 6 and 12 months] and well within the accepted limit of 500mL over three months as stipulated by the KEMRI–Wellcome Trust Research Programme, Kilifi, Kenya guidelines for the maximum volume per participant and other international guidelines. Where possible routine care and study-specific samples will be combined in a single blood draw.

Table 2 Maximum blood volumes in children per bodyweight category

|                                                          | 5.5 b –
<10 kg | 10 –
<15 kg | >=15kg –
<12/13 yrs | >=12/13 years
(~>=27.7kg) a |
|----------------------------------------------------------|------------------------------|----------------|------------------------|-------------------------------------------|
| Weight in Kg in weight category                          | <10 kg                       | <15 kg         | <12/13 yrs             |                                           |
| Maximum weight in Kg in weight category                  | <10                          | <15            | <22.2                  |                                           |
| Screening study volume (mL)                              | 0.25                         | 0.25           | 0.25                   | 0.25
(2x20) + (5x15)                   |
| Cohort study Days 1, 3, 7, 14, 21, 28, 42 (mL)           | 7x2.5=17.5                   | 7x5=35         | 7x7.5=52.5             | = 115                                     |
| 3 month follow-up visit (mL)                             | 2.5                          | 5              | 5                      | 15                                        |
| Cumulative volume by 3 m (mL)                            | 20.25                        | 40.25          | 57.75                  | 130.25                                    |
| Cumulative volume by 3 m, safety limit (mL) c | 27.5                         | 50             | 75                     | 138.5                                     |
| 6 & 12 month follow-up visits (mL)                       | 2x2.5=5                      | 2x5=10         | 2x5=10                 | 2x15=30                                   |
| Cumulative volume by 12 m (mL)                           | 25.25                        | 50.25          | 67.75                  | 160.25                                    |

a This is the minimum (1st percentile) expected bodyweight expected for 12 or 13-year-old girls (who are lighter than boys), the age of assent in Burkina Faso and Kenya respectively. Based on the 1st percentile for weight-for-age of 10 year olds and an average weight gain of 25% in girls between 10 and 12 years of age.

b This is the minimum expected bodyweight for a six months old child (the lower age threshold for inclusion in the study) based on the 1st percentile of the WHO weight-for-age growth reference

c Cumulative volume of blood that is considered safe in children for repeated blood draws taken for research purposes over a three month period (in addition to the blood taken for routine clinical care), based on a maximum of 5ml/kg body weight

Younger children below the age of assent (Burkina Faso 12 years, Kenya 13 years) will be excluded from the pharmacokinetic sampling to minimize the blood volume in younger children as the pharmacokinetic sample requires 5mL. Children below 10kg bodyweight will have 2.5mL instead of 20mL or 15mL blood draws taken during follow-up in addition to the finger/heel prick on Day-0 (250 uL) (a cumulative total of 20.25mL by over three months and 25.25 mL over 12 months). This ensures that even the lightest six months old children (the minimum age at enrolment) remain below the safety limit of 5mL/kg over three months (corresponding to a bodyweight of 4.1 kg for eight blood draws of 2.5 mL per sample) because the first percentile at the age of six months of the WHO weight-for-age reference is 5.5kg in girls. Similarly, the volume for children weighing 10- <15kg will be 5mL per draw, and 7.5mL for children weighing 15kg or more until the age of assent. At the age of assent (12 years in Burkina Faso and 13 years in Kenya), they are eligible for the nested malaria treatment trial and 20mL (Days 1 and 28) or 15mL (days 3, 7, 14, 21, 42) per sample will be taken, or 120.25mL over three months and within the 3-month safety limit of 138.5mL (based on the 1st percentile for weight-for-age of 10 year old and an average weight gain of 25% in girls between 10 and 12 years of age.). The cumulative volume by 12 months will be 130.25mL (see Table 2, above).

Figure 5: Maximum blood volume per bodyweight in children for research in addition to blood taken for routine clinical care

[figure not shown]

### 12.7.2 Benefits to study participants or society

By taking part in this study, participants will potentially benefit from close observations. Participants who do not attend scheduled appointments will receive reminders and active follow-up. Participants

experiencing illness between visits will be seen and treated free of charge as part of the study, although this is already routine practice in both countries.

There is a potential benefit to society as participation in the study will help investigators to obtain a better understanding of the impact of COVID-19 on people's health in malaria-endemic areas.

### 12.7.3 Risk to the population and study staff and biohazard containment

#### 12.7.3.1 *Biohazard containment to limit risks of SARS-CoV-2 transmission*

The design is based on practical considerations that both Kenya and Burkina Faso are implementing social distancing and stay at home strategies which restrict free movement and make home visits more challenging. The procedures for identifying a case and the subsequent isolation and management will follow local and national guidelines in each country, and the study will interfere as little as possible in the usual local investigation and management of COVID-19 cases unless this is deemed necessary to comply with the research team's responsibilities to provide adequate care to research participants.

As the transmission of SARS-CoV-2 and other respiratory droplet pathogens can occur through contact with respiratory droplets and contaminated surfaces, precautions will be employed by all personnel in the handling of all specimens for this study. Strict adherence to personal protection equipment (PPE) and other infection prevention and control (IPC) measures will be followed according to local guidelines in each country to minimize the risk of transmission of SARS-CoV-2. The recommended types of PPE per activity will follow national guidelines in Kenya and Burkina Faso. These are currently based on the WHO guidelines for 'Recommended type of personal protective equipment (PPE) to be used in the context of COVID-19 disease, according to the setting, personnel and type of activity' (see 16.6, Appendix VI. Personal protection equipment guidelines for study staff by risk category, page 85). All swabs and other biological samples will be taken by a trained study team member as per national standard operating procedures with strict adherence to these PPE guidelines. Also, to limit exposure in clinic waiting rooms, dedicated appointments will be made to collect clinical specimens.

Staff will be trained to remember to observe hand hygiene and standard precautions, including adherence to hand hygiene by washing with soap and water or using alcohol-based hand sanitizer immediately after removing gloves and other equipment and after any contact with respiratory secretions. Full personal equipment should be worn comprising of PPE suit, N95 mask, goggles or face shield, hair protection, while obtaining nasopharyngeal swabs for suspected cases and undertaking aerosol-generating procedures (e.g., bronchoscopy, elective intubation, suctioning, administering nebulized medications, dental procedures). The study-specific procedure will be undertaken in well-ventilated separate rooms or areas, such as dedicated tents that are away from the routine clinical areas.

For the safe transport of biological substances, see section 10.7.2, Shipping, page 48. For the local, within country, transport of dangerous goods and materials, including diagnostic specimens and infectious substances, we will follow by local Governmental Regulations.

#### 12.7.3.2 *Community sensitisation and public engagement for home visits*

Continuous community sensitisation and public engagement will be used, as per the national guidelines in each country to mitigate the risk to the staff and participants to allow home visits. Similar strategies are used by national Governments in each country for contact tracing.

### 12.7.3.3 *Transport arrangements*

Safe transportation can also include a car with three or fewer occupants where all the occupants, including the sick person, use facial masks. Public transport (matatus, buses) should not be used to transport sick individuals to the nearest isolation facilities as these are likely to propagate the spread of infection. If safe transport is not available, then a dedicated study vehicle with trained drivers and appropriate personnel and PPE will be dispatched to pick the patient. Trained drivers will be provided with face masks and other PPE and disinfectant to clean the cars after each trip. The study team is working in close collaboration with the Ministry of Health to arrange dedicated COVID-19 ambulances with oxygen supply and ambulance staff in full PPE for the transport of any patients requiring urgent hospitalisation.

### 12.7.4 Other ethical considerations

#### *Long term samples storage for future studies and shipment of samples to external laboratories*

With respect to applicable country regulations, written informed consent/assent will be sought from participants for long term storage of their samples for future research, which permits long-term storage of samples for 25 years in Kenya and 10 years in Burkina Faso. When consent for long-term storage for future research is not granted by the participant, the surplus sample volume will be destroyed following the completion of this study.

Informed consent will also be sought for the shipping of their samples to external laboratories overseas for relevant analyses. It will be clarified that the results of these assays will not be used for patient care.

## 12.8 ANCILLARY AND POST-TRIAL CARE

### 12.8.1 Health care during the trial

All care directly related to the proper and safe conduct of the trial, and the treatment of immediate adverse events related to trial procedures will be provided free of charge by the study in the study hospitals. The provision of ancillary care beyond that immediately required for the conduct of the trial will not be covered by the trial.

### 12.8.2 Trial insurance

The Liverpool School of Tropical Medicine and the London School of Hygiene & Tropical Medicine hold Public Liability ("negligent harm") and Clinical Trial ("non-negligent harm") insurance policies which apply to this study. This will include cover for additional health care, compensation or damages whether awarded voluntarily by the Sponsor, or by claims pursued through the courts. The liability of the manufacturer of the trial drugs is limited to those claims arising from faulty manufacturing of the commercial product and not to any aspects of the conduct of the study.

### 12.8.3 Post-trial care

The study budget is not in a position to fund post-study care.

## 12.9 EXPENSES REIMBURSEMENT AND INCENTIVES

The study will provide payment for all study drugs, study procedures, study-related visits and reasonable medical expenses that are incurred in study clinics or hospitals as a result of the study, including expenses for transport for any study-related visits including unscheduled visits in between scheduled visits to study clinics. The study will not cover the costs of any non-study related events, including scheduled or unscheduled surgery or trauma-related events (e.g. accidents, burns etc.) if this is not deemed to be related to the study by the principal investigators or their representative.

Table 3: Reimbursement of expenses and incentives provided by the study

| To Whom     | What                                                                                                           | Approximate Amount                              |
|-------------|----------------------------------------------------------------------------------------------------------------|-------------------------------------------------|
| Hospital    | Improvement of infrastructure where required                                                                   | up to ~\$10,000/hospital                        |
|             | Training of routine staff adult ward                                                                           | ~ \$3,000/hospital                              |
|             | Study procedure costs and study drugs and admission fees for inpatients                                        | ~ \$100,000/hospital                            |
| Participant | Travel expenses for the participant and for one accompanying person/caregiver.                                 | Up to ~\$10 per person per round trip*          |
|             | Average compensation for loss of daily wages for each day they are scheduled to come to the hospital or clinic | ~\$ 5 per day (excluding any travel expenses)** |

\* A fixed rate of 5,000 XOF/CFA or 950 KES (~ \$9 USD) will be given per visit for the combined compensation for the participant's or caretaker's time and travel expenses. In Kenya, the average travel expenses are about KES 400 (~\$4) per visit, however, in exceptional cases, higher amounts (>\$10) of travel expenses can be reimbursed if distance or transport modes requires this. This would need to be decided on a case by case basis, courtesy of the site PI/coordinator. In addition, they will receive ~\$5 USD per day for loss of daily wages for each day they are scheduled to come to the hospital or clinic (i.e. a total of about \$9 USD for travel and loss of daily wages).

## 12.10 DISSEMINATION AND APPLICATION OF THE RESULTS

### 12.10.1 Result dissemination and publication policy

Our research findings will be communicated to country-level stakeholders including the study participants, reproductive health and malaria programmes/national Ministries of Health, and the research partner institutions in Kenya and Burkina Faso, and to other national and international research partners, NGOs, technical agencies and implementing partners, donor organizations, WHO, UNICEF, Medicines for Malaria Venture (MMV) and Shin Poong Pharm. Co., Ltd, the licence holders of the FLU-PRO questionnaire (NIH) and the general public. We will use multiple communication strategies to reach each target audience, as outlined below. Specifically, we will

- Share results early with National policymakers and implementers (MOH Kenya and MOH Burkina Faso)
- Share results early with WHO's Global Malaria Programme (GMP) (prior to publication)
- Share results early with the Imperial College modelling group and any other COVID-19 modelling groups
- Share results early with international policy implementers and funders of malaria control programmes such as the President's Malaria Initiative (PMI)
- Present results at scientific planning meetings and international conferences
- Peer-reviewed publication with early access via pre-print servers for health sciences

<https://www.medrxiv.org/>

### 12.10.2 Impact

See section 3.2, Problem statement and Justification for the study, page 23, for potential impact.

### 12.10.3 Authorship and publications

Potential authors include all professionals that have participated in the study for a minimum of four of the 18 months. Authorship of any presentations or publications arising from this study will also be governed by the principles for authorship criteria of the International Committee of Medical Journal

Editors has designed. Disputes regarding authorship will be settled by the publications committee, with further involvement of the independent chair of the DSMB if so required. The manufacturer of the study medication will be provided with a draft of the manuscript but will have no role in the review, data interpretation, or writing of the article.

#### 12.10.4 Data Sharing Statement

We will encourage data sharing to ensure that the scientific potential of this study is maximized.

##### 12.10.4.1 Types of data

We anticipate that five different datasets will be generated by this project:

- An epidemiological data set containing cross-sectional data from the source population, i.e. including SARS-CoV-2 positive and negative patients, with and without malaria co-infection. This is estimated to include data from approximately 4000 to 5000 participants depending on the test positivity rate for SARS-CoV-2.
- A clinical and serological cohort dataset that includes approximately 708 COVID-19 patients with and without malaria
- An immunological cohort data set with all immunological parameters from a subset of approximately 180 participants
- An antimalarial treatment response data set involving the participants enrolled in the nested malaria treatment trial, including the corresponding safety data.
- A PK/PD data set on the sub-group of participants included in the pyronaridine-artesunate treatment component

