### 3.2.3 Does the choice of antimalarial treatment affect disease progression or the rate of seroconversion to SARS-CoV-2 infection?

Third, it is also important to know if the choice of antimalarial to treat malaria in co-infected patients affects the rate of seroconversion or disease progression. Most countries in sub-Saharan Africa, including Kenya and Burkina Faso, use artemether-lumefantrine as the first-line antimalarial for the case-management of uncomplicated malaria. Lumefantrine belongs to the group of aryl-amino alcohols like quinine, mefloquine, and halofantrine and does not have any anti-viral properties in-vitro ([name], MMV personal communication). Pyronaridine, as the artemisinin-based combination therapy (ACT) pyronaridine-artesunate (PA), is increasingly being rolled-out in sub-Saharan Africa as second-line treatment, or as an alternative to artemether-lumefantrine as part of a rotational or mosaic first-line treatment strategy to delay the onset of the development of drug resistance. It remains to be determined if antimalarial treatment with pyronaridine-artesunate provides any additional clinical benefit compared to treatment with artemether-lumefantrine in COVID-19 patients who are co-infected with malaria and require antimalarial treatment.

In humans, pyronaridine is slowly eliminated and has extensive tissue binding, including in the lung. PK/PD modelling suggests that pyronaridine when provided as a standard 3-day treatment course of pyronaridine-artesunate, could potentially provide 28 days of anti-viral cover based on their predicted pulmonary exposure ([name] and [name], personal communications, LSTM).

Assumptions of the study include that the in vitro effects of pyronaridine against SARS-CoV-2 will translate to an in vivo effect and a benefit in human

participants and that pyronaridine reaches concentrations in human tissues, including the lungs, that have a viral suppressive effect. However, the exact distribution of pyronaridine within the respiratory tract, and whether these in vitro findings will translate into clinical benefit, is unknown.

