### 11.1.3 Nested malaria treatment trial

Approximately 54 participants in Kenya are expected to have malaria (15% of 354) and will be enrolled in the nested treatment study comparing AL vs pyronaridine-artesunate (1:1). The corresponding number in Burkina Faso is 88 (25% of 354). Thus 142 pooled across the two countries. A study of 142 participants has 80% power to detect a 22.2% absolute increase in viral clearance by day-7 from 20% in the artemether-lumefantrine arm to 42.2% in the pyronaridine-artesunate arm ( $RR=2.11$ ), assuming a 5% loss to follow-up by day 7 (134 completers) (two-sided  $\alpha=0.05$ ). The 20% viral clearance rate by day=7 in the control arm (artemether-lumefantrine) is based on a previous trial.

Similarly, a sample of 142 participants has 80% power to detect a 50% relative decrease ( $RR=0.50$ ) or increase ( $RR=1.50$ ) in the cumulative seroconversion rate by day 14 from 50% in the artemether-lumefantrine arm (control arm) to either 25% or 75% in the pyronaridine-artesunate arm, assuming a 10% loss to follow-up (128 completers). The seroconversion rate of 50% by day 14 is based on previous observational COVID-19 studies in China.

Although the nested malaria treatment trial will be exploratory in nature, the study design includes the option to conduct interim analyses as part of the emergency response to the pandemic to ensure that promising findings can be shared early (see 11.2.5.3, Interim analysis and early stopping rule for efficacy, page 59).

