#### 11.2.8 Pharmacokinetic analysis

Compartmental Population Pharmacokinetic Modelling will be performed using Monolix 2018R2 to establish the pharmacokinetic profile throughout the population and relate to covariates, including patient sex, weight, BMI and malaria/COVID-19 disease status. The pharmacokinetic analysis will also be performed on quantified drug concentrations within saliva samples to establish drug distribution to this compartment and related to predicted lung concentrations using Physiologically Based Pharmacokinetic (PBPK).

Pharmacokinetic-Pharmacodynamic modelling will be similarly performed using compartmental analyses Monolix by linking drug exposure to drug effects quantified through SARS-CoV-2 expression from nasal swabs collected at similar time points to blood samples. Other covariates relating to patient symptoms and recovery status and time will be studied in parallel and separate analyses to investigate any potential PKPD interactions.

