#### 16.9.7 Pharmacokinetic studies

**Collaborating institutions and contact persons:** Liverpool School of Tropical Medicine: [name], [name] and [name]. University of Liverpool: [name].

**Objective:** To characterise the pharmacokinetic parameters of pyronaridine in patients, assess variables that influence overall pharmacokinetic exposure and build a pharmacokinetic-pharmacodynamic relationship between pyronaridine exposure and SARS-CoV-2 burden.

**Rationale:** Pyronaridine has displayed efficacy against SARS-CoV-2 virus in preliminary studies with an IC50 of 0.73µM ([name] lab, LSTM). The clinical efficacy of this compound hasn't been established yet, and a pharmacokinetic study will allow for studying the pharmacokinetic-pharmacodynamic drivers of pyronaridine efficacy in the clinic. The study will also allow for studying disease effects upon its pharmacokinetic profile, particularly in patients who are co-infected with malaria. With a drug that is widely used in malaria within Africa and COVID-19 likely to spread further in the future, it is important to characterise the possible interactions between the two. Furthermore, unlike other antimalarial compounds such as chloroquine, amodiaquine, mefloquine and doxycycline, the pharmacokinetics of pyronaridine has not previously been investigated in saliva. In the current study, saliva is being utilised as a surrogate for drug distribution into the tissues and fluids of the upper respiratory and digestive tracts which are a key site for SARS-CoV-2 transmission and ongoing viral replication. Studies with other antimalarials have also sought to utilise saliva as a readily accessible surrogate for plasma exposures to simplify downstream therapeutic drug monitoring. Therefore, the investigators propose to validate assays to determine conclusively whether substantive penetration of the drug into this matrix occurs in patients. If successful, these methods will be critically important to rationalise outcomes from the nested malaria treatment trial and to provide tools for longer-term evaluation of the exposure-response relationship of pyronaridine as it relates to malaria and SARS-CoV-2 coinfection.

**Sample size:** All consenting individuals in the pyronaridine arm of the nested malaria treatment trial (~70).

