**Methods:** Blood, plasma and saliva samples will be collected from the patients for analysis using LC/MS-MS. Appropriate extraction methods will be chosen for pyronaridine as previously published depending on the analysed matrix. All analyses will involve at least one internal standard, precision tests and standard curves to characterise the lower and upper limits of quantitation for pyronaridine in each matrix.

The quantified levels of pyronaridine will then be fitted according to a compartmental pharmacokinetic model using Monolix 2018R2 through the IQRtools package in R. The pharmacokinetic models will aim at simultaneously fitting all data to characterise the PK properties of pyronaridine in patients infected with COVID-19 with or without malaria co-infection as well as calculating the drug's partitioning between plasma, blood and saliva. Using a pharmacometrics approach, the models will establish the pharmacokinetic profile of pyronaridine and assessing the effect of covariates including malaria-disease status and other administered compounds at the time upon drug exposure in the different analysed compartments (blood, plasma and saliva).

These pharmacokinetic models will aid in building pharmacokinetic-pharmacodynamic models to relate drug exposure to overall anti-viral activity through the simultaneous modelling of pharmacokinetic profile in blood, plasma and saliva and SARS-CoV-2 levels in swab and saliva samples.

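### The planned pyronaridine PK contrast by malaria status cannot be estimated because everyone sampled has malaria, and the PK/PD data set as described leaves out the AL arm's viral loads

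*Protocol*

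**What the plan says.** Section 16.9.7 gives the PK sample as "All consenting individuals in the pyronaridine arm of the nested malaria treatment trial (~70"). Its methods say the models will "characterise the PK properties of pyronaridine in patients infected with COVID-19 with or without malaria co-infection" and will assess covariates that include malaria-disease status. Section 11.2.8 likewise lists malaria/COVID-19 disease status among the PK covariates.

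For the PK/PD step, 11.2.8 plans "linking drug exposure to drug effects quantified through SARS-CoV-2 expression from nasal swabs". The data-sharing list in 12.10.4.1 describes the matching data set as "A PK/PD data set on the sub-group of participants included in the pyronaridine-artesunate treatment component". Neither 11.2.8 nor 16.9.7 mentions AL participants in connection with this model.

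The nested trial is 1:1. Its primary endpoint is SARS-CoV-2 clearance on day 7, and swabs are taken on the same days in both arms (4.3: days 1, 3, 7, 14, 21 and 28).

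**The concern.** There are two points, of different weight.

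**Malaria covariate.** A with-versus-without-malaria comparison of pyronaridine PK needs pyronaridine concentrations from people without malaria. The design appears to supply none, so a stated aim could not be delivered.

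**Exposure-response.** Viral load falls without pyronaridine. The sample size section itself assumes clearance "from 20% in the artemether-lumefantrine arm to 42.2% in the pyronaridine-artesunate arm", so a fifth of controls clear by day 7. If only PA participants are modelled, nobody has zero exposure. Natural decline and drug effect must then be told apart from differences in exposure between people who all took a standard three-day course. Those differences are not randomised, and the slow elimination of pyronaridine makes the drug effect change little over the swab period. Section 3.2.3 says the course "could potentially provide 28 days of anti-viral cover based on their predicted pulmonary exposure", which would span every swab. At stake is whether the exposure-response estimate is precise and credible enough to use.

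**Working it through.** **Plan's own figure.** 0.15 × 354 + 0.25 × 354 = 53.1 + 88.5 = 141.6; the plan says "Thus 142 pooled across the two countries". With "comparing AL vs pyronaridine-artesunate (1:1"), the PA arm is 142 / 2 = 71, which agrees with about 70. The number with PK data will be lower, because children below the age of assent are excluded from PK sampling (2.2.4, note p).

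**Can anyone without malaria contribute a pyronaridine concentration?** The possible routes are:

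- Entry to the nested trial: needs all cohort criteria (SARS-CoV-2) and confirmed malaria (6.2.3.1).
- RDT positive on the HRP2 band only: followed only if microscopy confirms asexual parasites (9.2.1.3).
- SARS-CoV-2 result turns out negative: course completed, no further follow-up (2.2.4, note n).
- Malaria-negative cohort member who later develops malaria: treated with AL (9.2.7).
- AL participant switched to PA after repeat vomiting (9.2.1.3) or recurrence (9.2.7): entered with malaria.

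Every route gives malaria = 1. A regression with an intercept, one other covariate and this indicator has rank 2 of 3, so the malaria effect has no estimate whatever the sample size.

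**How well does a PA-only fit identify the drug effect?** Take, for participant *i* at day *t*:

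log10 V = a_i − g·t − E·J_i(t) + error, with J_i(t) = ∫₀ᵗ C/(C + C50) ds,

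where *g* is natural decline and *E* the drug effect. Inputs from the protocol: half-life 16 days (product information in 16.7.1: 14 to 18), swab days 1 to 28, and 134 / 2 = 67 completers per arm. Assumed, because the protocol gives no values: starting C/C50 from 2 to 30, between-subject exposure CV 40%, residual SD 1 log10.

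Why the two terms overlap: by day 28 concentration is 2^(−28/16) = 0.297 of its start. At C/C50 = 30, the term C/(C + C50) moves only from 30/31 = 0.97 to 8.9/9.9 = 0.90. At C/C50 = 2 it moves from 0.67 to 0.595/1.595 = 0.37. The nearer this term is to constant, the more J resembles a multiple of *t*.

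Single-exponential kinetics, full schedule:

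| C/C50 | SE of E, PA only | SE of E, both arms | Ratio |
|---|---|---|---|
| 2 | 0.047 | 0.014 | 3.4 |
| 5 | 0.053 | 0.010 | 5.3 |
| 10 | 0.099 | 0.009 | 11 |
| 30 | 0.188 | 0.008 | 24 |

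The PA-only correlation between the estimates of *g* and *E* is −0.98 to −1.00. A repeat with fresh exposure draws gave 3.9 to 27 for the ratio.

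The product information describes two-compartment kinetics with a distinct distribution phase. Assuming that 80% to 90% of the initial level is lost with a half-life of 1 to 2 days (no values are given), the ratio falls to about 2 at C/C50 = 2 and about 5 to 8 at C/C50 = 30, roughly 2 to 6 overall. The correlation is then −0.92 to −1.00.

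**Simpler cross-check**, linear in exposure with n = 71 per arm, mean exposure 1 in PA and 0 in AL:

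SE/σ = 1/√(n·CV²) for PA only; 1/√(n·CV² + n/2) with AL.

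At CV 30%: 1/√6.39 = 0.396 against 1/√(6.39 + 35.5) = 0.155, a ratio of 2.6. At CV 15% and 50% the ratios are 4.8 and 1.7.

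**Confounding.** In a simulation with no drug effect (71 PA participants, exposure CV 30%, a prognostic factor explaining a quarter of the variance in decline and not adjusted for), an exposure-prognosis correlation of 0, 0.2 and 0.4 gave false-positive rates of 5%, 12% and 41%. These correlations are assumptions.

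**The case against.** **The PA-only restriction is not firmly fixed.** Section 12.10.4.1 is an anticipatory list for data sharing. The 70 in 16.9.7 is naturally the number with pyronaridine to measure, and neither 11.2.8 nor 16.9.7 excludes AL viral loads. Such detail could go in the SAP. This stands in part, so the second point is a cheap improvement to what the protocol describes rather than an outright error. It does not touch the first point: no SAP can create malaria-negative pyronaridine samples.

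**A reader might infer that drug effect cannot be separated from natural decline at all.** The calculations do not support that: PA-only standard errors are finite. Dose per kg also varies with the weight bands in 16.7.1, for example 360/24 = 15.0 mg/kg down to 360/45 = 8.0 within the two-tablet band. The problem is imprecision and confounding, not strict non-identifiability.

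**A reader might infer that 16.9.7 offers the PK/PD model as the tool for explaining the trial's outcomes.** In context, the methods said to be critically important for that are the saliva assays.

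**Disease status in 11.2.8 could mean severity, symptoms or parasite burden**, all of which vary. That is a fair reading of 11.2.8; the explicit with-or-without wording in 16.9.7 cannot be read so.

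**The analysis is peripheral.** PK/PD is not among the objectives in 4.3, and the nested trial is called exploratory. This limits the weight of the point.

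**Conclusion.** The first point is a definite internal contradiction. Section 16.9.7 promises a PK contrast by presence or absence of malaria in a sample where malaria is present by design. It cannot be produced, and this conclusion needs no assumption.

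The second point is a worthwhile improvement. As described, the PK/PD data set omits the concurrent zero-exposure arm that the trial already swabs. A PA-only fit can be done but is nearly collinear, imprecise and non-randomised. The size of the gain from adding AL data is uncertain: roughly 2- to 6-fold in the standard error with a distribution phase, and 4- to 27-fold with a single exponential, for C/C50 of 2 to 30 and exposure CV 40%. The upper figures should not be relied on, but the direction is the same in every version tried.

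The randomised comparison of day-7 clearance is unaffected. This is a should-fix item on a supporting analysis.

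**What to change.** 1. In 16.9.7, delete the wording on patients with or without malaria co-infection. In 11.2.8 and 16.9.7, replace malaria/COVID-19 disease status with measures that vary and are already collected, such as baseline parasite density and baseline viral load or WHO score.
2. In 11.2.8 and 16.9.7, state that the viral-dynamic PK/PD model is fitted jointly to both randomised arms. Natural decline is a shared parameter, and AL participants enter at zero pyronaridine exposure until any switch to PA. Because younger children have no PK samples, apply the same age limit to both arms in this model.
3. In 12.10.4.1, add AL-arm viral loads to the PK/PD data set.

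The cost is slightly more modelling work. No participant, visit, swab or assay is added, since AL swabs and viral loads are already planned on the same days.
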